
##### Executive functions and learning

Rey Auditory Verbal Learning Test (RAVLT) (Rey, 1941): a measure of list learning (immediate recall) and long-term memory (delayed recall). It provides a Total Recall score (the number of correct words learned over five trials, score range: min = 0, max = 75, higher score = better outcome), a Delayed Recall score (the number of correct words recalled after a 20-min delay, score range: min = 0, max = 15, higher score = better outcome), Recognition score (the score calculated by subtracting false positives from recognition, score range: min = 0, max = 15, higher score = worse outcome).Digit spans forward and backward—task from the Wechsler Adult Intelligence Scale—revised (WAIS-R) (Wechsler, 1981): a measure of short-term memory and working memory (separate score for forward and backward, the length of the maximum span correctly repeated, score range: min = 1.0, max = 7.0, higher score = better outcome).Spatial spans forward and backward (Corsi, 1972): a measure of non-verbal short-term memory and working memory (separate score for forward and backward, the length of the maximum span correctly answered, score range: min = 1.0, max = 7.0, higher score = better outcome).Ravens Colored Progressive Matrices (RCPM) (Raven and Raven, 2003): a measure of problem-solving skills, logical reasoning, attention, and ability to learn (the total number of correct answers, score range: min = 0, max = 36; higher score = better outcome).Trail Making Test (TMT) (Stuss et al., 2001): a measure of attentional abilities. It provides a total score in time (score range: min = n/a, max = 300 s; higher score = worse outcome), a Part A score in time (score range: min = n/a, max = 300 s; higher score = worse outcome), a Part B score in time (score range: min = n/a, max = 300 s; higher score = worse outcome), a difference score (score range: min = n/a, max = n/a; higher score = worse outcome) and a ratio score (score range: min = n/a, max = n/a; higher score = worse outcome).Attention—Attention Network Test (ANT) (Fan et al., 2005): a measure of the effects of cues and targets within a single reaction time task. The task provides RTs for congruent and incongruent trials, either cued or non-cued. Three scores are derived from these trials: orienting, alerting and detection, all involved in attention. These scores reflect different components of executive functions (score range: min = n/a, max = n/a; higher score = worse outcome).

##### Lifestyle questionnaires

Caregiver Burden Questionnaire (Zarit et al., 1980): questionnaire filled only by the caregiver as a measure of the degree of burden, made with a 29-item self-report inventory (score range: min = 0, max = 84; higher score = worse outcome).Communication Aphasia Test (CAT): Disability Questionnaire (Swinburn et al., 2012): questionnaire filled by both the individual with PPA and their caregiver as a measure of communication difficulties. Questions cover reading, writing, speaking, and understanding (score range: min = 0, max = 64; higher score = worse outcome).Communication Confidence Rating Scale for Aphasia (CCRSA) (Cherney et al., 2011): questionnaire made of 10 questions to answer with a percentage scale (from 0% to 100%) filled by both the individual with PPA and their caregiver as a measure on communication confidence (score range: min = 0, max = 100; higher score = better outcome).Clinical Dementia Rating Scale (CDR) (Morris, 1993): questionnaire filled only by the caregiver as a measure of dementia severity and progression in FTD (score range: min = 0, max = 24; higher score = worse outcome).Dementia Quality of Life Scale (DEM-QOL) © Institute of Psychiatry King's College of London (Smith et al., 2005): questionnaire filled by both the individual with PPA and their caregiver (score range: min = 28, max = 112; higher score = better outcome).Exercise Questionnaire (in-house questionnaire developed by [name]) : qualitative questionnaire filled by both the individual with PPA and their caregiver describing the individual with PPA's level of weekly physical activity.Instrumental Activities of Daily Living (IADL) (Lawton and Brody, 1969): questionnaire filled out only by the caregiver (score range: min = 0, max = 8, higher score = better outcome)Language Experience and Proficiency Questionnaire (LEAP-Q) (Marian et al., 2007): questionnaire filled only by the caregiver to rate the individual with PPA's proficiency in other languages using an 11-point Likert scale (0–10).Progressive Aphasia Severity Scale Questionnaire (PASS) (Sapolsky et al., 2014): a measure of the severity and progression of language deficits in patients with PPA filled by the caregiver. The scale evaluates 13 linguistic domains (each with scores ranging from 0 to 3, higher score = worse outcome). These domains include articulation, fluency, syntax and grammar, word retrieval and expression, repetition, auditory comprehension, single-word comprehension, reading, writing, functional communication, conversation, turn-taking during conversation, and language generation.Patient Health Questionnaire (PHQ-9) (Kroenke et al., 2001): questionnaire filled by both the individual with PPA and their caregiver (score range: min = 0, max = 27; higher score = worse outcome).Pittsburgh Sleep Quality Index (PSQI) (Buysse et al., 1989): consists of 19 self-rated questions and five questions rated by the bed partner or caregiver, grouped into seven component scores: subjective sleep quality, sleep latency, sleep duration, habitual sleep efficiency, sleep disturbances, use of sleeping medications, and daytime dysfunction (score range for each component: min = 0, max = 21; higher score = worse outcome).Resilience Evaluation Scale (RES) (van der Meer et al., 2018): questionnaire with eight questions filled by both the individual with PPA and their caregiver (score range: min = 0, max = 36; higher score = better outcome).Survey of Autobiographical Memory (SAM) © Baycrest, 2012 (Palombo et al., 2013): questionnaire made of 26 items to answer using a 5-point Likert scale (1: completely disagree to 5: completely agree) covering four memory domains (episodic, future, semantic, and spatial) filled by both the individual with PPA and their caregiver (episodic score range: min = 0, max = 45; higher score = worse outcome; future score range: min = 0, max = 30; higher score = worse outcome, semantic score range: min = 0, max = 30; higher score = worse outcome, spatial score range: min = 0, max = 30; higher score = worse outcome).

Surrogate outcome measures include several MRI sequences, genetic sequencing, and biomarkers. As shown in Table 1 and Figure 1, MRI exams and biomarker samplings are performed at T1, T4, and T7.

#### Neuroimaging

MRI protocols for structural and resting-state functional MRI will follow those established by the Alzheimer's Disease Neuroimaging Initiative (ADNI). This large, multi-center, and multi-manufacturer study offers standardized protocol implementations that can be harmonized across different MRI devices, ensuring consistency and comparability of imaging data across various research sites. Each participating site will adapt the ADNI-3 protocol to their specific scanner hardware and software while maintaining core acquisition parameters to ensure harmonization. Structural and functional connectivity will be measured using the following methods based on the ADNI-3 protocol (representative parameters):

T1-weighted structural MRI (MPRAGE): Used for volumetric and cortical thickness analysis. ADNI-3 representative parameters: TR = 8.8 ms, TE = 1.9 ms, flip angle = 20°, FOV = 256 × 256 mm^2^, voxel size = 1 × 1 × 1 mm3, 176 slices, no gap.T2-weighted structural MRI: Fast spin echo (FSE) sequence for visualization of white matter lesions and anatomical delineation. ADNI-3 representative parameters: TR = 3,000–3,700 ms, TE = 80–100 ms, voxel size = 1 × 1 × 1 mm3, 176 slices.FLAIR imaging: Included to assess white matter hyperintensities/microvascular lesions, as recommended by ADNI-3.Diffusion tensor imaging (DTI): Used for structural connectivity analysis. ADNI-3 representative protocol: 232 × 232 × 160 mm at 2 × 2 × 2 mm, TE = 71 TR=3,300, three shells (b = 500,1,000, 2,000 s/mm^2^), 112 total diffusion-weighted directions, scan time ≈ 7 min 10 s.Resting-state functional MRI (RS-fMRI): Used for functional connectivity analysis. ADNI-3 representative sequence: 2D EPI sequence with SENSE acceleration, in-plane resolution = 3.3 × 3.3 mm^2^, 64 × 64 voxels; TR = 2,500 ms, TE = 30 ms, flip angle = 75°; slice thickness = 3 mm; 250 time points, scan time ≈ 11 min.

##### Neuroimaging analysis

###### Gray/white matter ratio

Using SPM12 (Wellcome Department of Imaging Neuroscience Group, 2014) Tissue Volume utility (Malone et al., 2015), we will segment MPRAGE images into gray and white matter and calculate each subject's gray/white ratio within the region of interest (ROI) beneath the tDCS site. This involves adjusting for volume changes and correcting for intensity non-uniformities.

###### Region-of-interest (ROI) volumetric analysis

ROI volumetric analysis following the automated segmentation of the MPRAGE using MRI Cloud (Mori et al., 2016).

###### Cortical thickness

FreeSurfer software (Fischl, 2012) will measure cortical thickness within the ROI underlying the tDCS site. The Advanced Normalization Tools software (ANTs) (Avants et al., 2009) will map MNI volumetric coordinates to FreeSurfer's surface-based coordinate system.

###### Total intracranial volume (ICV)

ICV will be computed for each subject using SPM12 (Wellcome Department of Imaging Neuroscience Group, 2014) Tissue Volume utility (Malone et al., 2015) to measure the volumes of gray matter, white matter, and CSF, which are then summed to calculate ICV. This helps account for potential differences in ICV between men and women and its potential impact on tDCS effectiveness.

###### DTI image analysis

MRICloud (Mori et al., 2016) will automatically preprocess and segment diffusion-weighted images, focusing on DTI scalars such as fractional anisotropy and mean diffusivity, and segment them into 169 regions of interest. We will concentrate on areas of the language network underlying the tDCS site.

###### RS-fMRI analysis

MRICloud (Mori et al., 2016) will preprocess resting-state fMRI scans, coregistering them with MPRAGE scans, and parcel them into 283 segments using a multi-atlas fusion label algorithm. Standard preprocessing includes corrections for motion and physiological noise, and average time courses are extracted and normalized for 78 ROIs. Correlations between region pairs are calculated and transformed using the Fisher z-transformation.

#### Genetic factors

Saliva samples will be collected for processing to extract DNA. Saliva samples will be stored at room temperature and processed in batches.

Saliva samples will be collected using the OG-100 Oragene collection kit. DNA will be extracted using standard methods, and genotyping will be performed at the Johns Hopkins DNA Diagnostic Laboratory utilizing Taqman assays and an ABI7900HT apparatus.

##### Genetic sequencing

DNA extracted from saliva samples will be analyzed to identify specific gene polymorphisms that may influence neuroplasticity and cognitive function. The gene polymorphisms of interest include:

Brain-derived neurotrophic factor (BDNF) gene: The Val66Met polymorphism, resulting from a G/A substitution at codon 66, leads to either a valine (Val) or methionine (Met) substitution. Individuals may carry one of three variations: Val/Val, Val/Met, or Met/Met.Catechol-o-methyl transferase (COMT) gene: The Val158Met polymorphism, involving a G/A substitution at codon 158, results in Val/Val, Val/Met, or Met/Met variations.Apolipoprotein E (ApoE) gene: Variants of the ApoE gene include ε2, ε3, and ε4 alleles, with possible combinations such as ε3/ε3, ε3/ε4, or ε4/ε4.

#### Biomarkers

Blood samples will be collected and processed to extract relevant biomarkers.

Blood will be drawn from veins in the forearm using a standardized protocol. Blood is collected into two pre-chilled lavender-top EDTA tubes and one room-temperature red-top serum tube.Samples are inverted immediately after collection and stored on ice or at room temperature as appropriate. Processing and freezing are completed within 60 min of collection.

##### Biomarker analysis

The following biomarkers will be analyzed in the blood sample to measure the concentration of each:

Neurofilament Light Chain (NfL)Serum TauAmyloid-β (Aβ)

### Statistical analysis

This trial investigates whether combining tDCS targeting the left IFG with a tailored spoken naming and spelling therapy improves language abilities and communication in individuals with PPA, with expected benefits extending to untrained tasks and lasting up to 3 months. It also aims to identify predictors of treatment response.

The primary outcomes will be analyzed using a general crossover formulation that considers each follow-up time point, the effects of treatment (s-tDCS vs. a-tDCS), phase (P1 or P2), and their interaction. For each participant, the data will include the order of treatments (s-tDCS in phase 1 and a-tDCS in phase 2, or vice versa) and changes in accuracy from before to after each phase for phonemic accuracy (during spoken naming) and letter accuracy (during spelling) of trained items.

The general crossover analysis will estimate parameters such as intervention effects in each phase and the overall average intervention effect. Estimates of these effects, standard errors, and confidence intervals will be calculated using the generalized estimating equation (GEE) method with robust variance estimation to account for correlations among repeated outcomes across different time points and phases within an individual. *P*-values will be exact and derived by comparing the estimates to the distribution calculated by permuting the order of intervention assignment across patients.

To address potential carryover effects inherent in the within-subject crossover design, a period-by-treatment interaction term will be included in the GEE model. A significant interaction will indicate possible carryover. In this case, follow-up sensitivity analyses will be conducted such as restricting analyses to Period 1 only, to confirm whether the treatment effect is robust. Washout adequacy will also be examined based on baseline performance at each phase.

To identify the predictors of differential effects of tDCS vs. sham on primary outcomes, we will separately analyze clinical (PPA variant, severity of impairments), neural (functional and structural), genetic, cognitive, and demographic (age, sex) factors, as well as lifelong language experience (e.g., bilingualism) factors. We will employ a model comparison approach, evaluating each predictor type based on effect size and cross-validated R-squared variance. By sequentially adding each predictor type, we will measure the variance contributed by each factor and establish a threshold for acceptable variance from each factor. To account for multiple comparisons across the range of predictors tested, we will apply False Discovery Rate (FDR) correction using the Benjamini-Hochberg procedure (Benjamini and Hochberg, 1995). This approach controls the expected proportion of false positives among the predictors identified as significant, ensuring a balanced trade-off between Type I error control and discovery potential in the context of exploratory modeling.

Using cross-validated, R-squared model selection minimizes the need for extensive adjustments for multiple comparisons. We will also assess the significance of the remaining factors by comparing them to the bootstrap distribution of sorted t-statistics under the null hypothesis that no factors predict the tDCS vs. sham effect. This final model will help us identify individuals who demonstrate a statistically significant difference between the effects of tDCS and sham treatment.

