### Data collection

Demographic characteristics will be collected at the enrollment session (T0) after obtaining informed consent and the eligibility screening. Medical records will also be collected at that point. Saliva samples will be collected at baseline (T1) and blood samples will be collected before P1 (T1), at 3 months after P1 [i.e., before P2 (T4)], and at 3 months after P2 (T7).

Each participant will undergo clinical, cognitive, and language assessments at seven time points throughout the study: before intervention period 1 (P1) (T1), after P1 (T2), 4 weeks after P1 (T3), and 3-month after P1 [T4, also serving as before intervention period 2 (P2)], after P2 (T5), 8 weeks after P2 (T6), and at 3-month after P2 (T7). Figure 1 provides an overview of the study time course. Primary and secondary outcome measures will be consistently assessed for each participant, and the assessor will remain blinded to the participant's treatment allocation throughout all visits. Surrogate outcomes [Magnetic Resonance Imaging (MRI) scans] will be obtained before P1 (T1), at 3 months after P1 [i.e., before P2 (T4)], and at 3 months after P2 (T7).

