Following the T1 assessment, the therapy level for each participant is determined based on their performance, and they remain at that level for all subsequent study periods. For each participant, four random lists are generated, each containing 20 items designated for treatment in Period 1, 20 for generalization measurement in Period 1, 20 for treatment in Period 2, and 20 for generalization measurement in Period 2. All lists are matched for the above-specified psycholinguistic factors, including AoA, frequency, and word length. Participants assigned to Level 2 are also probed on items from Level 1 at each assessment to help track general decline throughout the trial.

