#### Primary outcome measures

The primary outcome measure will be the change in performance between time points, as measured by phonemic accuracy (during spoken naming) and letter accuracy (during spelling) of trained items. Phonemic and letter accuracy will be calculated on a scale of 0–100%, with a higher number reflecting higher accuracy, using the Phonology analysis and Spelling analysis tools in Open Brain AI (Themistocleous, 2023).

At each assessment time point, participants undergo a comprehensive evaluation that includes the NaSp spoken naming and spelling task, which serves as the primary outcome measure. The task consists of 80 stimuli corresponding to the Level 1 stimuli previously outlined in the Therapy Stimuli section (along with 80 items included in Level 2 for identified participants). Accuracy on trained items is then computed separately.

The assessor presents all the words in the list. For each noun, participants attempt to name the item orally and then write their answer. No feedback is given, as some items serve as generalization items for either P1 or P2. After assessing the nouns, the same procedure is applied to the verbs.

All spoken and written responses are recorded. Spoken responses will be transcribed manually using the International Phonetic Alphabet, and written responses are captured using a smart pen (Symphony Smartpen by Livescribe, n.d.) to ensure accurate data collection. Both the spoken and written responses will be typed into a scoring document.

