This study population consists of individuals living with lvPPA or nfvPPA. Individuals living with svPPA are intentionally excluded, which we acknowledge limits the generalizability of the findings. However, this decision was based on both theoretical and empirical considerations. svPPA is characterized by profound semantic deficits, resulting in degraded word meaning and impaired object knowledge, which distinguish it from the phonological and graphemic impairments seen in lvPPA and nfvPPA (Gorno-Tempini et al., 2011; Sepelyak et al., 2011). These semantic deficits have been shown to reduce responsiveness to therapies targeting lexical retrieval and limit the generalization to items beyond those that have been trained. In prior work, individuals with svPPA demonstrated learning for trained items but failed to generalize the gains (Tsapkini et al., 2018; Roncero et al., 2019), a finding echoed in recent reviews (Norata et al., 2023). Individuals living with svPPA have been shown to respond better to interventions focusing on semantic knowledge and “look, listen, repeat” methods (Suarez-Gonzalez et al., 2021), or following stimulation of temporal areas (Teichmann et al., 2016), which is not the focus of this trial. By focusing on lvPPA and nfvPPA, the present trial targets populations with stronger evidence of responsiveness and generalization, enabling a more rigorous evaluation of tDCS as an adjuvant to lexical retrieval therapy.

The NaSp therapy protocol itself is an adaptation of previous work, refined specifically to target spoken naming and address prior limitations as the previous study focused on spelling. This updated protocol enhances the potential therapeutic effect for individuals with PPA, especially through its adaptability. Specifically, NaSp enables the tailoring of task difficulty to meet the needs of each participant, aligning with the principles of precision medicine. However, a limitation in the creation of the therapy lists is that trained and untrained items are not individualized; baseline performance does not influence the selection process. This lack of item-specific customization could, in some cases, obscure the therapy's effect, as the trained list may predominantly include words the participant already finds relatively easy, thereby minimizing measurable gains.

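### The primary change-score model leaves out starting accuracy on each period's trained list, which is measured before randomisation; this costs some precision but causes no bias

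*Protocol article*

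**What the plan says.** Primary outcome measures defines the outcome as a difference: "The primary outcome measure will be the change in performance between time points", scored from 0 to 100% on trained items. Statistical analysis says that the data for each participant are the treatment order and the "changes in accuracy from before to after each phase for phonemic accuracy (during spoken naming) and letter accuracy (during spelling) of trained items". The model "considers each follow-up time point, the effects of treatment (s-tDCS vs. a-tDCS), phase (P1 or P2), and their interaction". The only stated use of starting level is a check: "Washout adequacy will also be examined based on baseline performance at each phase".

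On lists, Therapy stimuli assigns "20 items designated for treatment in Period 1, 20 for generalization measurement in Period 1, 20 for treatment in Period 2", with a fourth list of 20 for generalisation in Period 2. All four are matched on age of acquisition, frequency and length. The Discussion concedes that "trained and untrained items are not individualized; baseline performance does not influence the selection process", and that a list of words already easy for the participant leaves little room for measurable gain.

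On timing, Data collection describes the 3-month visit after Period 1 as "T4, also serving as before intervention period 2 (P2"). Randomization and blinding places allocation after T1, and Primary outcome measures has the full stimulus set probed at every assessment.

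**The concern.** A participant's two trained lists can start at different accuracy, by chance and through measurement error at the baseline visit. A list that starts high, truly or through error, tends to show a smaller change. That variation enters the treatment contrast as noise unless the model accounts for it, and a pre-randomisation measurement that would do so is already collected.

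At 3 months there is a second source. Error common to the whole T4 visit (a good or bad day) raises the Period 1 change and lowers the Period 2 change, or the reverse. When the two changes are compared, that error counts twice. At stake is the precision of the primary comparisons.

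**Working it through.** **The plan's own figure.** Sample size gives power = Φ(es/√(rate/n) − 1.96) and 85% at n = 120, but no value for es or rate. Solving backwards, es/√(rate/n) = 1.96 + 1.036 = 2.996. So es/√rate = 2.996/√120 = 0.2735, or 2.996/√102 = 0.2967 with 15% dropout (120 × 0.85 = 102). The 85% can be neither reproduced nor refuted.

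**Notation.** A and B are the Period 1 and Period 2 trained lists; numbers are visits. A score is the sum of a person effect, a list effect (SD τ), a visit error shared by both lists (SD s_v) and a list-by-visit error (SD s_e). k is the drop in gain per point of higher true starting accuracy, which represents the ceiling. None of these values is in the document; all are assumptions.

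**Immediate contrast.** D = (A2 − A1) − (B5 − B4). The T1 covariate is C = A1 − B1.

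- Var(D) = 4s_v² + 4s_e² + 2k²τ²
- Var(C) = 2(τ² + s_e²)
- Cov(D, C) = −(s_e² + 2kτ²)
- Share of variance removed = Cov² / [Var(D) × Var(C)]

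With τ = 8, s_v = 3 and s_e = 6:

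| k | Cov² | Var(D) × Var(C) | Removed |
|---|---|---|---|
| 0 | 36² = 1,296 | 180 × 200 | 3.6% |
| 0.2 | 61.6² = 3,795 | 185.1 × 200 | 10.2% |
| 0.3 | 74.4² = 5,535 | 191.5 × 200 | 14.5% |

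A simulation (n = 102, 4,000 replicates) agrees: the SE falls from 1.308 to 1.285 at k = 0 (3.5%) and from 1.337 to 1.270 at k = 0.2 (9.8%). Varying the assumed SDs gives roughly 3–17%; this is a range, not a bound. If the 85% was computed for unadjusted change, power becomes Φ(2.996/√0.97 − 1.96) = 86% to Φ(2.996/√0.83 − 1.96) = 91%.

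**Three-month contrast.** D = (A4 − A1) − (B7 − B4). The T4 visit error has coefficient 2, and those of T1 and T7 have −1 each, giving 6s_v². Four separate visits would give 4s_v². List-specific error contributes 4s_e² either way, because A and B are different words. With f = s_v²/(s_v² + s_e²), the variance ratio is 1 + 0.5f: 1.00 at f = 0, 1.125 at 0.25, 1.25 at 0.5 and 1.50 at f = 1. If 85% had been computed for separate visits, power would be 81%, 76% and 69% at f = 0.25, 0.5 and 1. The assumed SDs give f = 9/45 = 0.2 and a ratio of 1.10. In the immediate contrast the four visits are distinct, so there is no loss. C contains no T4 error, so T1 adjustment does not remove this component.

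**Which covariate is safe.** The Objectives hypothesise generalisation to untrained items and effects lasting 3 months. At T4 the Period 2 list is still untrained. Suppose active stimulation in Period 1 shifts it by a lasting 3 points and the true effect is 5.

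- Change: the active-first group has D = 5 − (3 − 3) = 5 and the sham-first group −5; half the difference is 5.0. Adding T1 list accuracy leaves this at 5.0 in simulation.
- Post-phase accuracy with T1 covariate: the groups have 5 − 3 = 2 and −5; half the difference is 3.5.
- Post-phase accuracy with pre-phase covariate: 4.4 in simulation; with T1 and pre-phase covariates together, 3.9.

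If the shift fades completely during Period 2, change is also affected: 5 − (0 − 3) = 8 against −5, so (8 + 5)/2 = 6.5. Change therefore protects against a lasting shift only.

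**The case against.** The strongest reply is that this is an efficiency preference about a valid analysis. Robust GEE variance and permutation of treatment order give sound inference with or without a covariate. The article's list of terms need not be exhaustive, and the full analysis plan, which is not shown, may name covariates. The lists are matched on word properties and difficulty level is set from T1 naming with a 70% cut, so part of the starting variation is already controlled. The Discussion discloses the rest.

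Most of this stands and limits the point to precision. It does not remove it: change is the stated outcome, starting level appears only in the washout check, and matching on word properties does not equalise what an individual can name.

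Three stronger readings are tempting and are not supported:

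- **That the trial falls short of 85% power.** The variance input is said to come from comparable crossover studies and may already reflect change scores.
- **That one T4 score is both endpoint and baseline.** The trained lists differ by period, so only visit-level error is shared, and only at 3 months.
- **That change should be replaced by post-phase accuracy adjusted for the pre-phase value.** With pre–post correlation r between the list differences, the variance ratio is (1 + r)/2, so r = 0.5 would take 85% to about 93%. That gain assumes a baseline untouched by treatment, and the T4 baseline follows randomisation.

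**Conclusion.** The point holds as a modest loss of precision. The direction is secure: a pre-randomisation covariate related to the change reduces variance, apart from the small cost of estimating its slope. The size is not secure, because the documents give no SDs or correlations: about 3–17% of the variance of the immediate contrast under assumed SDs. The shared T4 visit adds between nothing and 50% to the variance of the 3-month contrast, with the upper end reached only if all error is visit-wide. No bias in the planned analysis and no error in the stated 85% follows from this point.

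**What to change.** Keep before-to-after change as the primary outcome. Before unblinding, prespecify as covariates T1 accuracy on that period's own trained list, entered as the participant's mean over the two lists and the deviation of each list from that mean. Use T1 phonemic accuracy for the spoken outcome and T1 letter accuracy for spelling, from the level the participant trains on. Refit the same model in every permutation, so that estimate and p-value correspond.

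Do not enter T4 accuracy as a primary covariate or drop the subtraction in the primary model. A model of post-phase accuracy can be a named sensitivity analysis. It avoids the double-counted T4 visit error but is open to a shift in the Period 2 list, so the two should be read together.

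Leave list generation as it is: changing it now would give earlier and later participants differently built lists. The cost is a sentence or two in the analysis plan and one or two degrees of freedom; no new data are needed.
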